### Blinding

Blinding of parents and professionals to allocation is not possible during the intervention period, including the T8 and T12 assessment. To ensure unbiased long-term outcomes, the T24 assessments are blinded. These assessments are carried out by T24-HEADS PPTs, who are unfamiliar with the history of the infants they are measuring. Furthermore, we instruct parents in the invitation letter and a poster at the assessment location, not to mention group allocation to the assessor.

### Interventions

#### *Randomised controlled trial*

Helmet therapy: parents of participants allocated to the helmet therapy group were asked to make an appointment at one of the three collaborating institutes for helmet therapy. First a (paediatric) physician was consulted to confirm diagnosis and exclude contraindications. Subsequently, the orthotist provided care as usual; he constructed the custom-made helmet, supplied information about introducing the helmet to the infant, regular wearing instructions and instructions about cleaning of the helmet and general care. The helmet has to be worn for at least 23 hours per day from six to twelve months of age.

No helmet therapy: Parents of participants allocated to the no helmet therapy group were asked not to start any treatment for the skull deformation of their child. In this group, recovery of deformation of the head was awaited by allowing spontaneous growth of the skull.

#### *Non-randomised controlled trial*

In the nRCT, parents were able to select a treatment for their child, that is, either helmet therapy or no helmet therapy. The choice was recorded afterwards when the child was twelve months old (T12).

### Data collection

The cohort study started with a baseline measurement at two to four months of age (T0). A follow-up measurement was performed in all children at 5 months of age (T5).

In the RCT, assessments took place at the age of 8 months (T8), 12 months (T12) and 24 months (T24) (Figure 1). In the nRCT the same assessments took place at T12 and T24. At T8 only a parental questionnaire was collected by mail.

Data were collected by the HEADS PPTs. During every assessment, the shape of the skull was measured, a motor assessment was carried out and both the parents and the HEADS PPTs were asked to complete a questionnaire. The HEADS PPT sent the data about each child to the researcher ([name]).

#### *Baseline characteristics*

Through the parental questionnaire at T0 and the parental questionnaire for late-enrolment at T5, information about background characteristics, medical characteristics and other possible prognostic factors were collected.

#### *Primary outcome*

The primary outcome is the transverse shape of the skull at 24 months, measured with PCM. The severity of deformational plagiocephaly was determined using the ODDI, and ear deviation (ED) was calculated to determine ear misalignment. The severity of deformational brachycephaly was determined by the CPI. A continuous outcome variable (change in score from pre- to post-test) as well as a dichotomous outcome variable will be used for analysis. The dichotomous variable distinguishes full recovery from no full recovery with a cut-off for full recovery of ODDI < 104% and CPI < 90%.

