### Sample size

The required sample size for the HEADS RCT, based on a significance level of 5%, power of 90% and a difference in mean improvement of at least 4 ODDI-points (SD 6 ODDI-points) was calculated as 72 infants (36 in each arm). Assuming a maximum estimated loss-to-follow up of 25%, we needed to include 96 children in the RCT.

In 2008, a preliminary study was performed into the feasibility of an RCT on helmet therapy for skull deformation. Of the parents of 61 children with a skull deformation, 39% agreed to participate in a study as described in the patient information and verbally clarified. In the light of this information, the size of the current study region was chosen and the inclusion period was estimated.

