### Statistical analyses

Data analyses will be performed using SPSS 18.0. A statistical significance level of 0.05 will be used and missing values will be imputed with multiple imputation [41].

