#### *Randomised controlled trial*

At T5, characteristics of the RCT population will be described. In a subsequent analysis, the intervention and control group will be compared with respect to prognostic factors using the independent samples *t*-test or the chi square test. The representativeness of the RCT population will be determined by comparing baseline demographic and clinical characteristics of the RCT population with those of the total eligible population at T5. Both the change score (continuous variable) and the success of recovery (dichotomous variable) will be compared between groups on an intention-to-treat basis. After analysis of covariance (ANCOVA), both multiple regression analyses (change score) and logistic regression analyses (success of recovery) will be carried out with predictor variables to control for confounders. Finally, a per-protocol analysis will be performed.

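### The primary outcome has no single deciding variable, testing order or alpha rule: two to four tests at 0.05, with family-wise error of 9.75% to 18.5% if independent

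*Protocol article*

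**What the plan says.** Under Primary outcome, the protocol article states: "The primary outcome is the transverse shape of the skull at 24 months, measured with PCM". It then lists the measures: "The severity of deformational plagiocephaly was determined using the ODDI, and ear deviation (ED) was calculated to determine ear misalignment", and "The severity of deformational brachycephaly was determined by the CPI". On how they are analysed it says: "A continuous outcome variable (change in score from pre- to post-test) as well as a dichotomous outcome variable will be used for analysis". Recovery in its yes-or-no form has "a cut-off for full recovery of ODDI < 104% and CPI < 90" (both limits in per cent), so it uses ODDI and CPI but not ED.

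Under Statistical analyses there is one general rule: "A statistical significance level of 0.05 will be used". The subsection on the randomised trial adds: "Both the change score (continuous variable) and the success of recovery (dichotomous variable) will be compared between groups on an intention-to-treat basis".

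The Sample size section is the only place that singles out one measure. Its calculation is "based on a significance level of 5%, power of 90" per cent, for a difference in mean improvement of 4 ODDI-points with SD 6. It does not declare ODDI change to be the deciding test. The Abstract speaks only of head shape at 24 months.

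**The concern.** A 5% level protects the primary question only if one test answers it, or if a rule links several tests. Here neither holds. A significant result on any of the listed variables could be called a positive primary result, and the plan does not say what follows if they disagree.

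Disagreement is a real possibility. Under Eligibility criteria, an infant can enter the randomised trial on ODDI alone, on CPI alone, or with a mixed form. A benefit on one index and none on the other is therefore plausible. Full recovery requires both indices to fall below their limits, so it can also diverge from either change score.

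The Abstract and the Discussion expect the results to influence treatment and reimbursement policy, so an ambiguous primary result would matter.

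**Working it through.** **Figures in the plan.** The article gives no family-wise error rate. Its only level is 0.05. The related figure is the sample size: alpha 5%, power 90%, difference 4, SD 6, giving 36 per arm, 72 in total, and 96 after 25% loss.

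- Check, two-sided: n per arm = 2 × (1.960 + 1.282)² × 6² / 4² = 47.3, so 48 per arm. That is 96 before any loss, so 72 is not reproduced.
- At 80% power: 2 × (1.960 + 0.842)² × 36/16 = 35.3, so 36 per arm, which matches the stated 72.
- One-sided 5% at 90% power needs 39 per arm, which does not match either.
- The loss step does reproduce: 72 / 0.75 = 96.

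The 90% versus 80% discrepancy is a separate matter. It is noted here because it affects any power restated below.

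**How many primary tests?** I count outcome variables only, not the adjusted and per-protocol analyses of each.

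- Two: one change score (ODDI) and full recovery.
- Three: ODDI change, CPI change and full recovery.
- Four: the same three plus ED change.

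**Family-wise error, each test at 0.05, independent:** 1 − 0.95^k.

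| Tests | If independent | Bound under any dependence |
|---|---|---|
| 2 | 1 − 0.95² = 9.75% | 10% |
| 3 | 1 − 0.95³ = 14.3% | 15% |
| 4 | 1 − 0.95⁴ = 18.5% | 20% |

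**With correlation.** The tests are not independent, because recovery is built from ODDI and CPI. The documents give no correlations, so these are assumptions. I simulated the null with 36 per arm, recovery derived from ODDI and CPI, and an assumed 25% recovery rate.

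| ODDI–ED correlation | Other two correlations | Two tests (ODDI, recovery) | Four tests |
|---|---|---|---|
| 0 | 0 | 9.3% | 17.8% |
| 0.5 | 0 | 8.9% | 16.5% |
| 0.7 | 0 | 9.6% | 16.5% |
| 0.8 | 0.3 | 8.7% | 14.7% |
| 0.9 | 0.5 | 8.3% | 13.3% |

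For three tests, equicorrelated normal statistics give 13.9% at correlation 0.2, 12.5% at 0.5 and 10.9% at 0.7. Across readings and assumptions the range is about 8% to 18%.

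**Direction.** These rates are two-sided. A false positive in favour of helmets has about half the probability: with four independent tests, 1 − 0.975⁴ = 9.6%, against 2.5% for one test.

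**Price of three co-primaries.** Holm's first step is 0.05/3 = 0.0167. At 36 per arm and 4/6 ODDI-points, power at that level is about 67%. At 0.05 it is about 81% (normal approximation). For 90% power at 0.0167, n per arm = 2 × (2.394 + 1.282)² × 36/16 = 60.8, so 61 per arm. That is 122 analysed and 122 / 0.75 = 163 recruited.

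**The case against.** The strongest objection concerns the count. A reader might infer that the plan commits to four primary tests and hence to an 18.5% error rate. The documents do not support that as fact. Both the outcome and the analysis sections speak of one continuous variable. ED is not in the recovery definition and is not named in the analysis of the randomised trial. Only two comparisons, a change score and recovery, are explicit there. This stands, and 18.5% is the top of a range. Even the most lenient reading allows up to 9.75% under independence, nearly double the stated level.

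A second objection is that testing order and alpha rules are commonly left to a statistical analysis plan, which is not shown. That holds for the mechanics of a correction. It does not hold for which variable is primary, which the protocol should fix. The article also says that it describes the planned statistical analysis, and it places the two forms on an equal footing.

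A third objection is that ODDI change suits this population imperfectly. Infants with brachycephaly alone enter on CPI with no minimum ODDI and may have little asymmetry to correct. This also stands. It bears on the choice of remedy and must be stated as a cost.

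It would also go too far to infer that the investigators intend to report whichever result is most favourable. Nothing in the document suggests it.

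**Conclusion.** The point holds. As written, the plan has several co-equal primary tests and no rule for deciding between them, so the stated 5% does not describe the error rate of the primary question.

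The figures rest on each listed variable being tested two-sided at 0.05, and on any single significant result counting as success. The rates under dependence also rest on correlations and a recovery rate that the documents do not give. The firm part is the missing deciding variable. The size of the inflation depends on how the Primary outcome section is read, and that uncertainty is part of the defect.

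**What to change.** Before any 24-month outcome data are analysed by arm, name one deciding primary variable in the outcome and analysis sections. Unblinding is not a usable deadline: according to the Randomisation and Blinding sections, parents, professionals and the allocating researcher already know the allocation, and only the 24-month assessors are blinded.

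**Preferred.** Make the change in ODDI from 5 to 24 months the primary variable, since the trial was sized on it. Test CPI change and then full recovery at 0.05, each only if the preceding test is significant. Report ED as an estimate with a confidence interval. This holds the family-wise error at 5%.

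The change is one of wording and needs no extra data. It has two costs:

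- Infants admitted on CPI alone may contribute little ODDI change, which could dilute the primary effect. The article does not give their share.
- A brachycephaly effect is confirmatory only if ODDI is significant.

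**Alternative.** If the sponsor wants CPI change or full recovery to be able to succeed alone, keep ODDI change, CPI change and full recovery as co-primaries under a Holm correction. Restate the power at the reduced alpha: about 67% for ODDI at the first step with 36 per arm. For 90%, 163 recruits would be needed, against the planned 96 and the 84 recruited so far.

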#### *Secondary outcomes*

Secondary outcomes are 1) satisfaction of the parents and HEADS PPT with skull shape, face and body (5-point Likert scale); 2) psychomotor development (a modified Gesell assessment, at regular well-baby clinic visits) [37]; 3) motor domain of Bayley Scales of Infant Development (BSID III) [38]; 4) anxiety level of parents (Spielberger State-Trait Anxiety Inventory, Dutch version) [39]; 5) parental concerns about the child’s future, possible teasing and uncertainty about the child’s appearance (5-point Likert scale); 6) quality of life (Infant Toddler Quality of Life Questionnaire (ITQOL-SF47) [40]) and 7) parental satisfaction with treatment.

#### *Compliance*

The questionnaire at T12 assessed whether parents were compliant with the therapy to which their child was assigned. Also recorded, was whether parents switched groups, and if they did, the age this happened and the reason for it. The helmet providers also collected start and end dates of helmet therapy given to infants in the RCT. Furthermore, helmets in the RCT of the HEADS study are equipped with a logging device (LoD). The LoD measures the number of hours a helmet is worn per week (therapy compliance) and will be used to determine a dose–response relationship. The LoD was attached to the helmet and data were sent to the researcher after the invention period.

In both groups, parents were asked at T12 whether they provided extra care to treat the skull deformation of their child, such as the use of positioning devices, performing exercises with their child or applying various additional therapies.

#### *Determination of costs*

Cost data were collected alongside the effectiveness study. Both medical costs and indirect costs incurred by parents because of diagnostic work-up and treatment were recorded. Indirect costs were collected with the help of a diary completed by parents during the intervention period. Costs are being determined for both the RCT and the nRCT.

### Sample size

The required sample size for the HEADS RCT, based on a significance level of 5%, power of 90% and a difference in mean improvement of at least 4 ODDI-points (SD 6 ODDI-points) was calculated as 72 infants (36 in each arm). Assuming a maximum estimated loss-to-follow up of 25%, we needed to include 96 children in the RCT.

In 2008, a preliminary study was performed into the feasibility of an RCT on helmet therapy for skull deformation. Of the parents of 61 children with a skull deformation, 39% agreed to participate in a study as described in the patient information and verbally clarified. In the light of this information, the size of the current study region was chosen and the inclusion period was estimated.

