## Discussion

The HEADS trial is the first study to present an RCT on the long-term effects of helmet therapy compared to no helmet therapy in infants with moderate to severe skull deformation. The HEADS study started as a cohort study for infants aged two to four months, and continued as an RCT after the first follow-up assessment at the age of five months. In parallel with the RCT, a non-randomised controlled trial (nRCT) was carried out. This extensive cohort study will provide excellent opportunities to study the determinants of skull deformation. Outcomes of the RCT and the nRCT will provide objective information about treatment options for the parents of affected children. With this information, an informed decision can be made whether to start helmet therapy or not. Additionally, outcomes from the cost-effectiveness study are expected to influence future treatment and reimbursement policies.

Recruitment in RCTs is often a challenge and it is common that trials fail to reach their target sample size [42]. In the RCT of the HEADS study, enrolment also proved more difficult than expected. During the recruitment period, it gradually became clear that only 21% of the parents of eligible infants gave consent for the RCT (Figure 1). This is half of the 39% enrolment rate predicted in the preliminary study, and questions the validity of a preliminary study. A much longer recruitment period is needed to recruit the calculated sample size of 96, necessary in case of a maximal loss to follow-up of 25%.

However, most parents refusing participation in the RCT are willing to enrol in the nRCT. Figure 1 shows that only 21 participants who were eligible for participation in the RCT or nRCT were not recruited, implying that almost the complete group of eligible patients at T5 (n = 331) from the original cohort was followed in the HEADS study. This emphasizes the advantage of the nested RCT design; due to their participation in the cohort study, participants are already committed to the study once the RCT and nRCT recruitment starts.

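### The sample size sentence claims 90% power for 36 infants per arm, but its own inputs give about 80%, and the target of 96 carries the error forward

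*Protocol article*

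**What the plan says.** The Sample size section of the protocol article sets out the whole calculation. It takes a 5% significance level, "power of 90% and a difference in mean improvement of at least 4 ODDI-points (SD 6 ODDI-points) was calculated as 72 infants", split equally into 36 per arm. It then adds the loss allowance: "Assuming a maximum estimated loss-to-follow up of 25%, we needed to include 96 children in the RCT". The Statistical analyses section repeats the level ("A statistical significance level of 0.05 will be used"). Neither section says whether the test is one- or two-sided, and neither gives a baseline SD, a correlation between assessments or any variance reduction. The Primary outcome section defines the continuous outcome as a change score, which matches the SD being given beside a difference in mean improvement.

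The Discussion uses the target again when it judges recruitment: "A much longer recruitment period is needed to recruit the calculated sample size of 96". The Population section reports 84 infants recruited to the RCT at the time of writing. That count is provisional (Figure 1 caption), and the trial is ongoing.

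**The concern.** Difference, SD, significance level, power and number per arm are tied by one formula, so any four fix the fifth. A difference of 4 with SD 6 is a standardised difference of 4/6 = 0.667. At 90% power and a two-sided 5% level that calls for nearly 50 per arm, so 36 looks too few.

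What is at stake is the declared type II error at the difference the trial was sized for. If the other inputs are right, that error is about 20% at the planned loss, not 10%. The 96 is also the benchmark against which the Discussion judges recruitment, and the article expects the results to bear on treatment and reimbursement policy. Readers who rely on the published design figure would credit the trial with more sensitivity to a 4-point benefit than it has.

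**Working it through.** **Inputs** (Sample size section): difference "a difference in mean improvement of at least 4 ODDI-points", so δ = 4; "SD 6 ODDI-points", so σ = 6; level 5%; power 90%; 36 per arm; loss 25%. Assumptions: two-sided test, independent groups, equal allocation, and σ as the between-infant SD of the change score.

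**Formula** (normal approximation): n per arm = 2 (z for α + z for power)² (σ/δ)², with (6/4)² = 2.25.

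**Does the plan's figure come out?**

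| Setting | Calculation | n per arm | Total | t-test n per arm |
|---|---|---|---|---|
| Two-sided, 90% | 2 × (1.960 + 1.282)² × 2.25 = 47.3 | 48 | 96 | 49 (total 98) |
| Two-sided, 80% | 2 × (1.960 + 0.842)² × 2.25 = 35.3 | 36 | 72 | 37 (total 74) |
| One-sided, 90% | 2 × (1.645 + 1.282)² × 2.25 = 38.6 | 39 | 78 | 40 (total 80) |

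The stated 72 appears only in the two-sided 80% row.

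**Power at 36 per arm.** The standard error of the difference is 6 × √(2/36) = 1.414, and 4/1.414 = 2.828.
- Two-sided, normal: Φ(2.828 − 1.960) = 80.7%. With the noncentral t: 79.7%.
- One-sided: 88.2% (normal), 87.6% (t).

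**What would make 36 per arm give 90%, two-sided?**
- With σ = 6, the difference would be 1.414 × (1.960 + 1.282) = 4.58 points (normal), or 4.65 by t-test (power 90.0%).
- With δ = 4, the SD would be about 5.2.

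**Loss allowance.** 72/0.75 = 96, so this step is right. For 90% power on the stated inputs it would be 96/0.75 = 128, or 98/0.75 = 130.7, so 131 (t-test).

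**Power over loss to follow-up** (two-sided t-test, δ = 4, σ = 6, fractional arm sizes used as they stand):

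| Randomised | Loss | Evaluable | Per arm | Power |
|---|---|---|---|---|
| 96 | 25% | 72.0 | 36.0 | 80% |
| 96 | 10% | 86.4 | 43.2 | 86% |
| 96 | none | 96.0 | 48.0 | 90% |
| 84 | 25% | 63.0 | 31.5 | 74% |
| 84 | 10% | 75.6 | 37.8 | 82% |
| 84 | none | 84.0 | 42.0 | 86% |

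**The case against.** **A one-sided test.** Sidedness is not stated, and a one-sided 5% test has about 88% power at 36 per arm, not far from 90%. But it would need 78 to 80 infants, not 72, and nothing in the article points to a one-sided test.

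**Adjustment for baseline.** The RCT analysis section mentions ANCOVA, so a reader might infer that a T5–T24 correlation of about 0.5 rescues the claim: the ANCOVA variance is (1 + ρ)/2 = 0.75 of the change-score variance, and 48 × 0.75 = 36. The documents do not support this. The ratio assumes equal SDs at T5 and T24. A change-score variance of 36 = 2σ²(1 − 0.5) then requires a T5 SD of 6. ODDI is the longest over the shortest oblique diameter, so it cannot fall below 100%. RCT entry is capped at 113%. The largest possible SD on that range is 13/2 = 6.5, with half the infants at each end, so an SD of 6 is implausible. The article gives neither a T5 SD nor a correlation.

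**Which input is wrong.** A reader might infer that the design was certainly an 80% design mislabelled as 90%. The exact match at 72 makes that the likeliest explanation, but a misprinted SD (about 5.2) or difference (about 4.6) would reconcile the sentence too. This objection stands, and the fix leaves the choice to the sponsor.

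**How low power really is.** A reader might infer that the trial has 74% power and misses a 4-point benefit one time in four. That is only the worst case: 25% is described as a maximum loss, 84 is a provisional count, and the Discussion still names 96 as the number to recruit. This also stands, so power is given as a range. Multiple imputation is planned too, so the analysed set is not simply the completers.

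**Consequence.** The error alters no estimate, test or type I error, and a null result should be read from its confidence interval. That limits the harm, but it does not make the published power figure right.

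**Conclusion.** The sentence is wrong as written. At the stated difference, SD and level, 36 evaluable infants per arm give about 80% power, not 90%. The type II error at the design difference is about 20%, twice what is declared. On the same inputs 90% power needs 96 to 98 evaluable infants, a third more than 72. The enrolment target of 96 equals that lower figure only by coincidence, because the article derives it as 72 plus a loss allowance. It delivers about 90% only if no infant is lost.

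The conclusion rests on a two-sided comparison of two independent means and on SD 6 being the SD of the change score. The first is conventional but not stated; the second follows from the wording of the sentence. A full protocol or analysis plan could show that a different SD or difference was used, but it could not make these printed figures agree.

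The article does not show that the trial must enrol 128 to 131 infants. That follows only if 90% is a binding target and the other inputs are correct.

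**What to change.** Reconcile the stated power with the stated inputs. Unless the SD or the difference is the misprinted figure, in which case correct that one, the Sample size section should say: 72 evaluable infants (96 randomised, 25% loss) give about 80% power to detect a 4-point difference with SD 6 at a two-sided 5% level, and 90% power for a difference of about 4.65 points.

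Add the power over a range of loss: about 80%, 86% and 90% for 96 randomised at 25%, 10% and no loss, and about 74%, 82% and 86% for 84 randomised. State that the test is two-sided. Do not defend the 90% by a baseline-adjusted analysis with an assumed correlation of 0.5.

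The cost is a sentence or two and a less favourable power figure. Correcting the statement requires no extra enrolment and no change to the analysis.

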#### *Randomised controlled trial*

Children aged 5 months with a moderate to severe skull deformation, measured by PCM are eligible for the RCT. PCM is a reliable, valid, non-invasive and easy-to-use method for measuring the shape of the skull [35,36]. To determine the severity of deformational plagiocephaly, the oblique diameter difference index (ODDI) is used. This is the ratio between the longest and the shortest oblique diameter, multiplied by 100%. Both diameters are located at 40° from the anterior-posterior line. A moderate to severe plagiocephaly is defined as 108% ≤ ODDI ≤ 113%. The severity of deformational brachycephaly is established with the cranio proportional index (CPI). This is the ratio between the width and the length of the skull and is considered to be moderate to severe when 95% ≤ CPI ≤ 104%. Mixed forms with ODDI > 106% and CPI > 92% are also included. Exclusion criteria are similar to those at T0.

At T5, children meeting RCT eligibility criteria can still enrol in the study (late-enrolment).

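### The planning SD of 6 ODDI-points is implausibly large for the infants admitted, and with 36 per arm it gives about 80% power, not the stated 90%

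*Protocol article*

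**What the plan says.** The Sample size section sets the error rates with "based on a significance level of 5%, power of 90" per cent and plans on "a difference in mean improvement of at least 4 ODDI-points (SD 6 ODDI-points) was calculated as 72 infants (36 in each arm"). It then adds: "Assuming a maximum estimated loss-to-follow up of 25%, we needed to include 96 children in the RCT". The article gives no source for the SD.

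The eligibility section for the randomised trial defines ODDI: "This is the ratio between the longest and the shortest oblique diameter, multiplied by 100" per cent. It sets the entry range for plagiocephaly: "A moderate to severe plagiocephaly is defined as 108% ≤ ODDI ≤ 113" per cent. Brachycephaly qualifies on CPI alone, which "is considered to be moderate to severe when 95% ≤ CPI ≤ 104" per cent. Mixed forms qualify with ODDI above 106% and CPI above 92%. The section on the non-randomised trial directs infants above the upper thresholds there.

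The Primary outcome section analyses the change from pre-test to post-test, with the outcome at 24 months. The Population section reports 84 infants recruited to the RCT. The Discussion concludes: "A much longer recruitment period is needed to recruit the calculated sample size of 96".

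**The concern.** The SD enters the sample size as a square, so it largely decides whether a given number of infants is enough. Here the index and the entry limits fix how far an infant can improve, and an SD of 6 is close to the largest value that range allows. The planning SD therefore looks incompatible with ordinary outcomes in this trial.

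The quoted sentence has a second fault that must be read with the first: its SD, sample size and power do not agree. If only the arithmetic is corrected, the target rises to about 128 to 131 on a doubtful SD. If only the SD is corrected, the power is still misstated for the inputs given. At stake is what power the trial has with the infants it has, and what the target of 96 in the Discussion rests on.

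**Working it through.** **Inputs.** Difference 4, SD 6, 5% significance, 90% power, 36 per arm and 25% loss (Sample size); ODDI floor 100% and entry cap 113% (eligibility); 84 recruited (Population). Sidedness is not stated; two-sided is assumed.

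**1. The plan's own figure.** Normal approximation: n per arm = 2·SD²·(z₁₋α/₂ + z_power)² / difference².
- 90% power: 2·36·(1.960 + 1.282)²/16 = 47.3, so 48 per arm, 96 evaluable, 96/0.75 = 128 recruited. The t-test gives 48.3, so 49 per arm, 98 evaluable, 131 recruited.
- 80% power: 2·36·(1.960 + 0.842)²/16 = 35.3, so 36 per arm, 72 evaluable, 72/0.75 = 96 recruited. These are exactly the plan's numbers.
- Power at 36 per arm: 4/(6·√(2/36)) = 2.83; Φ(2.83 − 1.96) = 80.7% (t-test 79.7%).
- One-sided 5% does not rescue it: 90% needs 39 per arm (78 evaluable, 104 recruited), and 36 per arm gives 88.2%.
- SD at which 36 per arm gives 90%: 4·√18/3.242 = 5.24 (t-test 5.16).

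**2. Limits on the SD.** Improvement is at most 113 − 100 = 13 points. If nobody worsens, the largest SD is 13/2 = 6.5. For an arm with mean improvement m, the limit is √(m·(13 − m)). With arm means 4 apart, a pooled SD of 6 is reachable only for control means of about 3 to 6, and then nearly every infant must improve by 0 or by 13 points.

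**3. Illustrative SDs of change** (assumed distributions; in the first four rows entry is uniform on 108–113%, so room to improve B has mean 10.5 and mean square 112.33)

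| Final ODDI | Variance | SD |
|---|---|---|
| Uniform between 100 and the entry value | 112.33/3 − 5.25² = 9.88 | 3.1 |
| Uniform 100–113, unrelated to entry | 25/12 + 169/12 = 16.17 | 4.0 |
| Half recover fully, half not at all | 112.33/2 − 5.25² = 28.60 | 5.3 |
| Uniform 100–120, unrelated to entry (47.5% of infants worsen) | 25/12 + 400/12 = 35.42 | 5.95 |
| Entry and final both uniform 100–113, unrelated | 2·169/12 = 28.17 | 5.3 |

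The last row allows for infants admitted on CPI with low ODDI. It reaches 5.3 only with no average improvement. With that wider entry range and final values uniform between 100 and the entry value, the SD is 2.9.

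**4. What 84 infants give.** 84·0.75 = 63 evaluable, about 31 per arm (31.5 used). Two-sided t-test at 5%, difference 4:

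| SD | Power with 84 recruited | Per arm for 90% | Recruited with 25% loss |
|---|---|---|---|
| 3 | 99.9% | 13 | 35 |
| 4 | 97% | 23 | 62 |
| 5 | 88% | 34 | 91 |
| 6 | 74% | 49 | 131 |

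A smaller target difference would change this. By the normal approximation, a difference of 3 with SD 4 needs 102 recruited, and a difference of 2 with SD 3 needs 128.

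**The case against.** The strongest reply is that SD 6 is mathematically possible. The limit without worsening is 6.5, the 113% cap applies only at entry, and nothing limits ODDI at 24 months. The mixed-form clause states no upper limit of its own, and brachycephaly entrants widen the baseline range. All this stands: a reader who infers that the entry criteria rule out SD 6 goes beyond the documents.

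A reader might also infer that the SD was taken from another population. The article does not say where it comes from, and a condensed article may leave the source to the full protocol, so its absence here is no fault.

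Thirdly, a generous SD is normally conservative. That would hold if the sample size had been computed from it at 90% power. It was not: on the stated inputs the target is too small, and 36 per arm at 90% corresponds to an SD of about 5.2, near the top of the plausible range.

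Finally, it is tempting to conclude that the 84 infants suffice and recruitment can stop. The documents do not support that. At SD 5 the power is 88% and about 91 recruits are needed. A smaller true difference needs more, and the primary outcome also covers CPI and a dichotomous full-recovery variable, whose power the ODDI SD does not settle. The Discussion itself says only that 96 are needed if the maximum loss occurs.

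**Conclusion.** The point holds as one of plausibility and internal consistency, not impossibility. SD 6 is implausibly large for the admitted range: ordinary patterns give about 3 to 5. The stated SD, size and power also cannot all be true: 72 evaluable and 96 recruited match about 80% power at SD 6, or 90% at an SD of about 5.2. The two faults pull in opposite directions, so the stated 90% may be roughly right or clearly too high, depending on the real SD.

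This rests on a two-sided test, on SD 6 meaning the SD of improvement, on the 113% cap also covering mixed forms, and on the assumed distributions shown. The arithmetic on power does not depend on the last two.

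**What to change.** Estimate the SD of ODDI change from the pooled, allocation-blind 24-month data already collected in the RCT. With equal arms the pooled variance includes (difference/2)², which is 4 at a 4-point difference, so the blind SD slightly overstates the within-arm SD (a blind 5 would mean √(25 − 4) = 4.6). Keep the 4-point target. In the Sample size section, withdraw the pairing of SD 6 with 90% power and state the power for the 84 recruited with 25% loss over SD 3 to 6: about 99.9%, 97%, 88% and 74%. Then align the Discussion's statement on 96 infants with the restated figure, without presuming that recruitment can stop.

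The cost is one blinded summary and a rewritten paragraph, with no extra infants for the check itself. The downside is that published planning figures must be withdrawn, and the restated power may fall below 90% if the observed SD is near 5 or above.
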